## Sample size

From baseline data, it is estimated that participating hospitals will have an average of approximately 150 stroke patients per year, that 5% of stroke patients in the control group will be prescribed tPA, and that the average co-efficient of variation across strata will be approximately 0.4. With 10 hospitals per group, the study will have 80% power with a 5% significance level to detect an absolute difference of 7% to 10% [67]. The subgroup analysis of hospitals with baseline tPA rate of <10% will also have similar power to detect this difference, as, although the number of hospitals per group will be smaller, the baseline tPA rate will also be lower.

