## Methods and design

The cluster randomised controlled trial will involve 20 hospitals in the Eastern Australian states of New South Wales (NSW), Victoria (VIC) and Queensland (QLD). Hospitals are the unit of randomisation and the unit of analysis. SCUs manage the majority of stroke patients across the Eastern states of Australia. Hospitals in the intervention group will receive a multicomponent multidisciplinary collaborative intervention based on behavioural principles as described by the Behaviour Change Wheel framework for the design and implementation of evidence-based practice [47]. The control hospitals will receive no intervention and are free to make practice changes of their own accord. Thus the study is an implementation effectiveness trial rather than an efficacy trial. The follow-up period will be two years post-baseline (*i.e*., Year 1 to 2 = baseline, Year 3 = intervention, Year 4 = follow-up), with an additional three months for measurement of functional outcomes for those thrombolysed in the final month of follow-up. Figure 1 describes the study design.

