##### *Stratified* randomisation

Hospitals will be stratified according to their stroke thrombolysis rates at baseline: very low (0% to ≤4.00%), low (>4.00% to ≤10.00%) or moderate (>10.00%). Baseline thrombolysis rate was considered important for the following reasons: A ‘very low’ thrombolysis rate suggests some impediments to thrombolysis, potentially limiting the ability of the site to respond quickly to the intervention. Sites categorised as having a ‘low’ thrombolysis rate may have the greatest potential for achieving change during the study, due to having substantial room for improvement. Conversely, a site with a ‘moderate’ baseline rate of thrombolysis may have limited opportunity to demonstrate further substantial improvement on the outcome measure.

Hospitals will be randomised at one time (effectively achieving allocation concealment) to either the intervention arm or the control arm with a 1:1 allocation ratio, using a computer generated stratified randomisation scheme in StatsDirect. Intervention hospital staff will not be effectively blinded to their allocation, in that they will be aware of their own involvement in intervention activities. There will be minimal interaction with control hospitals during the intervention phase.

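### The detectable difference of 7% to 10% cannot be reproduced from the stated sample-size inputs, which give about 5 to 5.5 percentage points at 80% power

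*Protocol article*

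**What the plan says.** The Sample size section of the protocol article gives one value for each input. On cluster size it says that "participating hospitals will have an average of approximately 150 stroke patients per year". On the control rate it says that "5% of stroke patients in the control group will be prescribed tPA", and on between-hospital variation that "the average co-efficient of variation across strata will be approximately 0.4". "With 10 hospitals per group", it then concludes that "the study will have 80% power with a 5% significance level to detect an absolute difference of 7% to 10" percent, citing a reference for the method.

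The subgroup of hospitals with a baseline rate below 10% is said to be one that "will also have similar power to detect this difference".

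Three other places bear on the calculation. Methods and design sets the calendar as "Year 1 to 2 = baseline, Year 3 = intervention, Year 4 = follow-up", so the outcome year supplies one year of patients. Stratified randomisation allocates hospitals "with a 1:1 allocation ratio" within three baseline-rate strata. Statistical methods names a stratified t-test on hospital-level summary data as the primary analysis.

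**The concern.** The inputs and the result are printed together and do not agree. The inputs are single values, the result is a range, and nothing in the section says what was varied to produce it. The low end of the range already lies above what the inputs imply.

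This is the only power statement for the primary outcome, so a reader will use it to judge which effects the trial could be expected to detect. Taken at face value, it suggests that a difference of 5 points is too small for the design, although the stated inputs give close to 80% power for it. If instead 7% to 10% is the correct result, then the published CV, control rate or cluster size does not describe what the investigators expected. The two cannot both stand without an explanation. The subgroup sentence refers to the same difference and so carries the same uncertainty.

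**Working it through.** **Inputs.** From Sample size: c = 10 hospitals per group, m = 150 patients per hospital, control rate p0 = 0.05, CV k = 0.4, power 80%, significance level 5%. One follow-up year comes from Methods and design, and 1:1 allocation from Stratified randomisation. Assumed: two-sided test, equal hospital sizes, same CV in both groups.

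**Formula.** Hospitals per group for comparing two proportions with a between-cluster CV:

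c = a + (z₀.₉₇₅ + z₀.₈₀)² × [p0(1−p0)/m + p1(1−p1)/m + k²(p0² + p1²)] / (p1 − p0)²

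Here (1.960 + 0.842)² = 7.849. The added term a is 1 for an unstratified design and 2 as an allowance for stratification.

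**Attempt to reproduce the plan's figure (a = 1).** The first term in the bracket is 0.05 × 0.95/150 = 0.000317 throughout.

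| Difference | p1 | p1(1−p1)/150 | 0.16(p0² + p1²) | Bracket | Hospitals per group |
|---|---|---|---|---|---|
| 5 points | 0.10 | 0.000600 | 0.002000 | 0.002917 | 1 + 7.849 × 0.002917/0.0025 = 10.2 |
| 7 points | 0.12 | 0.000704 | 0.002704 | 0.003725 | 1 + 7.849 × 0.003725/0.0049 = 7.0 |
| 10 points | 0.15 | 0.000850 | 0.004000 | 0.005167 | 1 + 7.849 × 0.005167/0.0100 = 5.1 |

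Ten hospitals per group therefore match 5% against 10%. Differences of 7 and 10 points would need about 7 and 5 per group. The plan's figure is not reproduced.

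**Solving for the detectable difference with c = 10.**

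| Method | Detectable difference, 80% power |
|---|---|
| Formula, no added cluster | 4.7 points |
| Formula, one added | 5.1 points |
| Formula, two added | 5.5 points |
| Noncentral t, 18 df | 5.1 points |
| Noncentral t, 14 df (three strata) | 5.2 points |

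**Power at the plan's own differences.** The noncentrality is the difference divided by √(bracket/10).

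| Difference | Noncentrality | Power, 18 df | Power, 14 df |
|---|---|---|---|
| 5 points | 2.93 | 79% | 78% |
| 7 points | 3.63 | 93% | 92% |
| 10 points | 4.40 | 99% | 98% |

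**Other readings of the same inputs.**
- One-sided 5%: 4.3 points.
- Between-hospital variance held constant across groups: 3.8.
- CV read as the total CV of observed rates: 3.8.
- CV converted to an intracluster correlation (0.16 × 0.05/0.95 = 0.0084, design effect 1 + 149 × 0.0084 = 2.25): just under 4.
- Two years of patients (m = 300): 4.5.
- CV at the edge of rounding (0.45): 5.8, or 6.3 with two added clusters.
- 7% and 10% read as intervention-group rates: differences of 2 and 5 points, with power of about 27% and 79%. Only the upper end would fit, and the text speaks of a difference.

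**What would give 7 to 10 points.** Changing one input at a time in the same formula:

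| Input changed | One cluster added | Two clusters added |
|---|---|---|
| CV | 0.52 to 0.64 | 0.48 to 0.60 |
| Control rate | 7.6% to 11.6% | 6.8% to 10.5% |
| Patients per hospital | 53 down to 23 | 67 down to 28 |

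**The case against.** The strongest reply is that the inputs are hedged. Hospital size and CV are both given as approximate averages, and the CV is averaged over strata whose baseline rates differ widely. A spread of inputs could naturally give a spread of results. The low end is indeed sensitive: a CV of 0.5 with two added clusters gives 7.3 points. A control rate of 7%, the approximate Australian rate quoted in the Background, gives 6.6 to 7.2 points at CV 0.4. Several inputs shifted together (control rate 5.49%, CV 0.449, an assumed effective 120 patients per hospital, two added clusters) give 7.1. The cited method was not available for this check, and an article condenses the full calculation, so an allowance such as one for unequal hospital sizes may have been made and not reported.

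This stands in part. It rules out saying that the result or an input must be a misprint, because an unstated allowance is a third possibility. It does not remove the mismatch. None of these variations comes near 10 points, and rounding the CV alone does not reach 7. Halving the effective hospital size to 75 gives only 6.2 points, or 6.7 with two added clusters. The section also reports no range of inputs.

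The second reply is that the discrepancy is conservative and changes no hospital number, test or decision rule. That is correct on the stated inputs, and a null result should in any case be read from its confidence interval. It limits the weight of the point to a correction of the text.

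A reader might also infer that the subgroup sentence is wrong in its own right. The article does not support that. It gives neither the number of hospitals in the subgroup nor their rate. With an assumed rate of 3% to 4%, power for 7 points is about 77-85% with 6 hospitals per group and 85-91% with 7, which fits the claim. Only about 5 per group, at 65-74%, falls clearly short.

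**Conclusion.** The stated range does not follow from the stated inputs. They imply about 5 to 5.5 percentage points at 80% power, and about 92-93% and 98-99% power at 7 and 10 points. This rests on a two-sided test, equal hospital sizes, one follow-up year and a common CV. A one-sided test or a second year of patients moves the answer further from 7.

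It would be tempting to conclude that the trial is underpowered or that 10 hospitals per group is the wrong number. Neither follows: on the printed inputs the sentence understates power. The concern would run the other way only if the true CV or control rate were higher than printed, and nothing in the article shows that. Which element is at fault cannot be settled from the article. This is a figure to correct or explain, not a flaw in the design.

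**What to change.** Retrieve and check the original calculation, then do one of the following.

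- **If the inputs are right:** restate the detectable difference as about 5 to 5.5 percentage points at 80% power, and add that power for 7 points is about 92%.
- **If 7% and 10% came from other inputs or an allowance** (a range of CVs, a different control rate, unequal hospital sizes): correct the inputs and state which values give each end of the range.

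The first option should not be adopted without the check, because it would overstate power if an input is the element at fault. In either case, state whether the 5% level is one- or two-sided, and recheck the subgroup sentence with the actual number of hospitals and the rate in that subgroup. The cost is wording only, with no change in hospitals, patients or analysis.

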## Statistical methods

Primary outcome: Analysis will involve cluster-level summary data. The difference in post-intervention thrombolysis rates between intervention and control groups will be compared via a two-stage approach to adjust for baseline thrombolysis rates, using a stratified *t*-test.

Secondary outcomes: The proportion of thrombolysed cases with good outcomes (mRS scores of 0 to 1) and the proportion with intracranial haemorrhage at each hospital will be compared to benchmarks (using a one tailed hypothesis test) and analogous methods to stopping rules for randomised clinical trials. Thresholds beyond which intervention is required will be calculated using one-sided hypothesis tests adjusted for annual checks. There will be intervention thresholds, beyond which quality assurance processes would be instituted, and stopping thresholds, beyond which tPA administration would be suspended until processes are reviewed. Because we are conducting three analyses, we have used the method of O’Brien-Fleming to determine significance levels for each of the three analyses (this method provides more stringent stopping criteria for early analysis). The appropriate significance levels are 0.0006, 0.0151 and 0.0471 for analysis 1, 2 and 3 respectively. Analysis will be intention to treat in that all individuals administered tPA should be included in the study database, and the denominator will be obtained directly from computerised hospital admissions data.

Secondary analyses: Given that there may be limited potential for hospitals with high baseline tPA rates to substantially further increase tPA administration, we will undertake a subgroup analysis of the primary outcome excluding hospitals with a baseline tPA of more than 10%.

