**Objectives:**

To test the effectiveness of a multi-component multidisciplinary collaborative approach compared to usual care as a strategy for increasing thrombolysis rates for all stroke patients at intervention hospitals, while maintaining accepted benchmarks for low rates of intracranial haemorrhage and high rates of functional outcomes for both groups at three months.

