**Methods and design:**

A cluster randomised controlled trial of 20 hospitals across 3 Australian states with 2 groups: multi- component multidisciplinary collaborative intervention as the experimental group and usual care as the control group. The intervention is based on behavioural theory and analysis of the steps, roles and barriers relating to rapid assessment for thrombolysis eligibility; it involves a comprehensive range of strategies addressing individual-level and system-level change at each site. The primary outcome is the difference in tPA rates between the two groups post-intervention. The secondary outcome is the proportion of tPA treated patients in both groups with good functional outcomes (modified Rankin Score (mRS <2) and the proportion with intracranial haemorrhage (mRS ≥2), compared to international benchmarks.

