## Aims

The study aims to test, using a cluster randomised controlled trial, whether a multi-component multidisciplinary collaborative approach can:

1. Increase the proportion of all stroke patients receiving thrombolysis at intervention hospitals, compared with control hospitals at follow-up (Primary Outcome);

2. Maintain best-practice benchmarks of 30% of patients achieving 3-month post-stroke modified Rankin scores of 0 to 1 (little or no disability) at both intervention and control sites (Secondary Outcome);

3. Ensure that the adverse event rate for major intracranial haemorrhage (parenchymal haematoma) in thrombolysed patients does not rise above best-practice benchmarks of 6% [19] in either intervention or control hospitals (Secondary Outcome).

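### The 6% haemorrhage and 30% good-outcome benchmarks are aims for the two groups, but the only formal comparison stated is at each hospital, where treated numbers are too small to say much about those aims

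*Protocol article*

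**What the plan says.** **The aims are set for the groups.** The abstract's Objectives speak of "maintaining accepted benchmarks for low rates of intracranial haemorrhage and high rates of functional outcomes for both groups at three months". Its Methods and design paragraph defines the secondary outcome through "the proportion of tPA treated patients in both groups with good functional outcomes", with haemorrhage alongside, each set against international benchmarks. In the Aims section, Aim 2 gives 30% with a modified Rankin score of 0 to 1 at intervention and control sites. Aim 3 asks that major haemorrhage "does not rise above best-practice benchmarks of 6% [19] in either intervention or control hospitals".

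**The test is set for the hospital.** Under Statistical methods (Secondary outcomes), "the proportion with intracranial haemorrhage at each hospital will be compared to benchmarks (using a one tailed hypothesis test"). Action thresholds "will be calculated using one-sided hypothesis tests adjusted for annual checks". Crossing one threshold starts quality assurance; crossing the other suspends tPA until processes are reviewed. No comparison of an arm with a benchmark is stated.

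**The volumes.** The Sample size section assumes that "participating hospitals will have an average of approximately 150 stroke patients per year, that 5% of stroke patients in the control group" receive tPA, with 10 hospitals per group and power "to detect an absolute difference of 7% to 10" percentage points.

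**The concern.** Aims 2 and 3 ask whether treating more patients keeps results acceptable across each arm. This is a live question: the Background reports that a Dutch cluster trial raised thrombolysis but saw more dependency afterwards in its intervention group. The plan as written produces up to 20 small hospital tests per outcome and no stated formal comparison at the level of the aim. A hospital that treats a handful of patients a year will seldom cross a threshold even if its true rate is well off the benchmark. It also cannot produce a precise estimate if its rate is good. A set of unremarkable hospital results would therefore say little about either aim.

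**Working it through.** **The plan's own levels.** The stated levels 0.0006, 0.0151 and 0.0471 reproduce as three-look O'Brien-Fleming values. With z_k = c·√(3/k) and c = 1.985, the two-sided levels are 0.0006, 0.0151 and 0.0471. Used one-sided over three equally spaced looks, they spend about 5.1% in total. The levels are not the problem.

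**Treated patients per average hospital** (from Sample size)
- Control: 150 × 5% = 7.5 a year, so 15 over Years 3 and 4.
- Intervention: 5% + 7 to 10 points = 12% to 15%. 150 × 12% = 18 and 150 × 15% = 22.5 a year, so 36 to 45 over two years.
- Per arm (× 10 hospitals): 150 control and 360 to 450 intervention over two years.

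These figures assume that the volumes hold in both years.

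**Can one hospital show haemorrhage below 6%?** With zero events the one-sided 95% upper limit is 1 − 0.05^(1/n).

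| n | upper limit with 0 events |
|---|---|
| 15 | 18.1% |
| 36 | 8.0% |
| 45 | 6.4% |
| 49 | 5.9% |

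The smallest n that works is ln(0.05)/ln(0.94) = 48.4, so 49. An average hospital does not reach it in two years.

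**Can one hospital detect an excess?** Exact binomial test of 6%, one-sided 5%, single analysis of two years' data, true rate 12%:

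| n | events needed | power |
|---|---|---|
| 15 | 4 | 10% |
| 16 (if 7.5 is rounded up each year) | 4 | 12% |
| 36 | 6 | 26% |
| 45 | 7 | 29% |

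**Can one hospital show good outcome above 30%?** The exact one-sided 95% lower limit reaches 30% with 9/15 (60%), 16/36 (44%) or 20/45 (44%). If the true rate is 40%, that happens 10%, 35% and 32% of the time. It is possible but demanding.

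**The same questions by arm, Years 3 and 4 pooled.** Power of a one-sided 5% test for 12% against 6%. The ICC is not in the documents, so 0.01 and 0.05 are assumed. The clustered figures come from beta-binomial simulation with 10 hospitals per arm and the critical count set under the clustered null.

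| arm | n | no clustering | ICC 0.01 | ICC 0.05 |
|---|---|---|---|---|
| control | 150 | 81% | 79% | 59% |
| intervention | 360 | 99% | 95% | 77% |
| intervention | 450 | 99% | 98% | 80% |

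Ignoring clustering, the upper limit falls below 6% with up to 4/150, 13/360 or 18/450 events. The lower limit for good outcome reaches 30% with 55/150 (37%), 123/360 (34%) or 152/450 (34%).

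**The case against.** **The aims can be read hospital by hospital.** Aims 2 and 3 are worded by site, and Methods and design makes the hospital the unit of analysis. The wording of the Aims alone would permit that reading. The abstract's wording, which refers to both groups twice, does not. It is also fair that the words tying the test to each hospital follow the haemorrhage clause directly; for good outcome the hospital reading is likely rather than certain.

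**An arm-level summary may sit in the analysis plan.** The passage describes monitoring and excludes no such summary, and an article may leave reporting detail to a fuller document. But the article does not stay silent on the unit of the test: it names one, and that unit answers the group aims poorly.

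**The hospital rules do a useful job.** This stands. Assuming cumulative data and three looks at the stated levels, a tripled haemorrhage rate (18%) would be flagged 88% to 93% of the time at intervention volumes and 48% to 62% at control volumes. Suspending tPA is a site decision, and pooling could hide one poor site.

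**A limit below 6% is stricter than the aim.** This also stands. An arm exactly at 6% meets the aim, yet its upper limit would fall below 6% at most 5% of the time. At a true 5%, and ignoring clustering, success is only 13% (n = 150), 14% (n = 360) and 20% (n = 450). The limit should be reported, not used as a pass mark.

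**Stronger readings that the document does not support**
- *Hospital tests can never show the aims.* That is strictly so only for haemorrhage, at average-volume hospitals, over one or two years. Good outcome above 30% is attainable, and some hospitals will treat more than the average.
- *The plan treats a non-significant hospital test as proof that a benchmark is maintained.* No sentence says this.
- *The three-look levels are wrong because only two looks exist.* Statistical methods says "Because we are conducting three analyses". The Secondary outcome section places annual haemorrhage checks in the intervention and follow-up phases, one year each, which makes two. A third is not excluded: three further months are allowed for functional outcomes, and the timeframe figure is not available here. No error is established.

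**Conclusion.** The point holds as a mismatch between the level of the aims and the level of the only stated formal comparison. At the plan's own average volumes, two years of data leave a hospital with zero haemorrhages at an upper limit of 6.4% to 18.1%, and give 10% to 29% power against a doubled rate. By arm, that power is about 81% (control) and 99% (intervention) ignoring clustering, or 59% and 77% to 80% at an assumed ICC of 0.05. The figures rest on average-sized hospitals, on control and target tPA rates as planned, and on one pooled analysis of Years 3 and 4. Severity is minor: the primary analysis is untouched, the site thresholds are sensible for their purpose, and existing adverse-event governance continues.

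**What to change.** Keep the hospital thresholds, described as governance triggers. Add one or two sentences, for example: *Aims 2 and 3 will be assessed by comparing each arm's haemorrhage and good-outcome proportions, pooled over Years 3 and 4, with 6% and 30%, using a method that allows for clustering by hospital. Each estimate will be reported with a one-sided 95% confidence limit; the aim is not judged by whether that limit clears the benchmark.*

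This needs no new data. The cost is that the result may be inconclusive, above all in the control arm. With a true haemorrhage rate of 3%, the chance that the two-year upper limit falls below 6% is 25% to 53% in the control arm and 53% to 91% in the intervention arm, across ICCs from 0.05 down to none. As a courtesy to readers, the same edit could state when each of the three looks takes place.

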#### Secondary outcome

The secondary outcomes include intracranial haemorrhage as defined by the SITS registry and functional outcomes at three months post stroke using the modified Rankin Scale (mRS) [55]. Intracranial haemorrhage events (parenchymal haematoma) will be identified from the TIPS database and will be monitored annually during the intervention and follow-up phases by the research team to ensure that it does not exceed international benchmarks [56]. Sites will be provided with additional support if benchmarks are exceeded. Monitoring of secondary outcomes will not interfere with established governance processes for reporting and monitoring of adverse events in the health system. Functional outcomes will be scored as good (mRS = 0 to 1) or poor (mRS = 2 to 6) by the treating clinician or stroke nurse. The mRS has demonstrated reliability and validity for use by clinicians and stroke nurses [57]. The percentage of tPA-treated stroke cases having a good outcome (mRS <2) at three months post stroke will also be monitored annually by clinical experts in the research team through the post-intervention NSF data collection.

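### The O'Brien-Fleming levels for outcome monitoring are on a two-sided scale while the tests are one-sided, and the text accounts for only two of the three analyses

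*Protocol article*

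**What the plan says.** The Statistical methods section compares each hospital's proportion with a good outcome, and its proportion with intracranial haemorrhage, with benchmarks "using a one tailed hypothesis test". It repeats the direction for the monitoring limits: "Thresholds beyond which intervention is required will be calculated using one-sided hypothesis tests adjusted for annual checks". Two kinds of limit are foreseen, one leading to quality assurance and one to suspension of tPA pending review.

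The section then turns to O'Brien-Fleming, with the reason "Because we are conducting three analyses" and the remark that "this method provides more stringent stopping criteria for early analysis". The result is fixed in numbers: "The appropriate significance levels are 0.0006, 0.0151 and 0.0471 for analysis 1, 2 and 3 respectively". It does not say whether these levels are one-sided or two-sided, and it gives no overall error rate for the monitoring.

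On timing, the Secondary outcome section says that haemorrhage "will be monitored annually during the intervention and follow-up phases by the research team". The Methods and design section gives the phases as "Year 3 = intervention, Year 4 = follow-up", after two baseline years, and adds three months to measure functional outcome in the last patients treated.

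**The concern.** Two things do not fit together. First, the three printed levels look like the familiar two-sided set for three looks, yet the section says twice that the tests are one-sided. A reader cannot tell whether 0.0006 is to be compared with a one-sided p-value or stands for a z-value of 3.43 applied in one direction. Second, annual checks over one intervention year and one follow-up year make two checks, while the levels are built for three.

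These numbers feed the limits at which a hospital is flagged. If the third analysis never takes place, the most lenient level, 0.0471, is never used and the rule is much more conservative than a 5% design.

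**Working it through.** **Inputs.** Levels 0.0006, 0.0151, 0.0471, three analyses and one-sided tests (Statistical methods). Benchmarks of 6% for haemorrhage and 30% for good outcome (Aims). About 150 strokes per hospital-year, 5% treated in controls, and a target difference of 7 to 10 percentage points (Sample size). Assumed, because the article does not state them: overall error 5%, equally spaced information, cumulative data at each look.

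**Step 1: where the printed levels come from.** The classical boundary for K looks is z_k = C·√(K/k), so z_k·√(k/K) should equal the constant C at every look.

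| Look | Level | z if two-sided | z·√(k/3) | z if one-sided | z·√(k/3) |
|---|---|---|---|---|---|
| 1 | 0.0006 | 3.432 | 1.981 | 3.239 | 1.870 |
| 2 | 0.0151 | 2.430 | 1.984 | 2.167 | 1.770 |
| 3 | 0.0471 | 1.985 | 1.985 | 1.674 | 1.674 |

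On the two-sided scale the product is constant within rounding, with C about 1.985. On the one-sided scale it is not. Even on the two-sided scale the match to 5% is only approximate: the exact constant is C = 2.004, which gives 0.0005, 0.0141 and 0.0451. The printed set has an overall two-sided error of 5.24%.

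**Step 2: levels for one-sided designs at 5% overall.**

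| Design | Look 1 | Look 2 | Look 3 |
|---|---|---|---|
| Classical, three looks (C = 1.710) | 0.0015 | 0.0181 | 0.0437 |
| O'Brien-Fleming-type spending, three looks | 0.0007 | 0.0161 | 0.0451 |
| Classical, two looks (C = 1.678) | 0.0088 | 0.0467 | n/a |
| O'Brien-Fleming-type spending, two looks | 0.0056 | 0.0483 | n/a |

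**Step 3: overall one-sided error of the printed levels.**

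- Three looks, levels used as one-sided p-value cut-offs: 0.0006 + 0.0147 + 0.0361 = 0.0514.
- Three looks, two-sided z-values applied in one direction: 0.0003 + 0.0074 + 0.0185 = 0.0262.
- Two looks only, first two levels as one-sided cut-offs: 0.0006 + 0.0147 = 0.0153.

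Each term is the probability of first crossing at that look.

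**Step 4: effect at one hospital at the first check.** Treated patients per hospital-year: 150 × 0.05 = 7.5, about 8; 150 × 0.12 = 18; 150 × 0.15 = 22.5, about 23. A value of 15 is added between them (10% of 150). The table gives the smallest number of haemorrhages whose exact binomial tail probability under 6% is at or below the level.

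| n | 0.0006 (printed) | 0.0015 (three looks) | 0.0088 (two looks) |
|---|---|---|---|
| 8 | 5 | 4 | 4 |
| 15 | 6 | 5 | 5 |
| 18 | 6 | 6 | 5 |
| 23 | 7 | 7 | 6 |

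The shift is never more than one event. For good outcome against 30%, the first-check cut-off is the same at 0.0006 and 0.0015 for all four sizes: at 8, 15 or 18 patients even zero good outcomes reaches neither level, and at 23 only zero does. The two-look level differs. With 18 patients, zero good outcomes has probability 0.7^18 = 0.0016, which misses 0.0006 and 0.0015 but passes 0.0088.

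**Step 5: counting the checks.** Annual monitoring over Year 3 and Year 4 gives one check at the end of each year, so two. The extra three months are described for functional outcome only. The text gives no date for a third analysis.

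**The case against.** The strongest defence has four parts.

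- **Overall error.** With three looks and the levels used as one-sided cut-offs, overall error is 5.1%, close to 5%. The levels also lie near the one-sided O'Brien-Fleming-type spending boundary (0.0007, 0.0161, 0.0451). This stands: with three looks, the sidedness mismatch does little harm on that reading.
- **Early strictness.** A reader might infer that the first check is far too strict. The documents do not support that. The article says that early stringency is what it wants from the method, and the first-check haemorrhage cut-off moves by at most one event. The gap looks large (0.0006 against 0.0088) only on the two-look reading.
- **Number of looks.** A reader might take it as established that only two checks exist. That is an inference. Figure 1, which gives the timeframe, is not shown in the text at hand, and a final analysis after the extra three months could be the third. If the two checks used the first and third levels, overall error would lie between 0.0471 and 0.0006 + 0.0471 = 0.0477, so the 1.5% holds only if the first two levels are the ones applied.
- **Claimed error rate.** A reader might say that the plan controls a different error rate from the one it claims. It claims none for the monitoring; the 5% in the Sample size section belongs to the primary outcome.

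The Secondary outcome section also leaves the health system's own adverse-event governance in place, so these limits are not the only safeguard. None of this removes the mismatch: the article fixes the numbers as appropriate, calls the tests one-sided, and leaves the reader to choose between overall errors of 5.1% and 2.6%.

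**Conclusion.** The point holds in a limited form. The printed levels have the classical three-look O'Brien-Fleming shape only as two-sided values, while the tests are one-sided. With three looks this is mainly a matter of labelling and small recalculation. The open question with more weight is the number of analyses: the described phases appear to give two, the levels assume three, and two checks at the first two levels would have an overall one-sided error of about 1.5%.

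These figures rest on an assumed 5% overall, equal information at each look and cumulative data. The matter concerns secondary-outcome monitoring and leaves the primary comparison untouched. It should be corrected, but it is not a critical flaw. Which limit should lead to suspension of treatment is not judged here.

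**What to change.** 1. Reconcile the Methods and design, Secondary outcome and Statistical methods sections on how many monitoring analyses there are and when each takes place. If there are three, give the date of the third and say whether it covers haemorrhage as well as functional outcome.
2. State the overall one-sided error rate for the monitoring, and say that the levels are one-sided p-value cut-offs.
3. Recompute the levels for that one-sided design and number of looks. If the yearly numbers of thrombolysed patients are unequal, use a spending function on the cumulative number.

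The cost is one short calculation and a sentence or two of text. No additional data collection is needed.
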